## Abstract

**Background:**

Severe acute malnutrition (SAM) is a major underlying cause of mortality among children. Around one third of the world’s acutely malnourished children live in India. The WHO recommends community-based management of acute malnutrition (CMAM) for managing children with SAM. In India, different states are implementing community-based SAM treatment programme, hereinafter called CSAM, using varieties of locally produced nutrient dense food items with different nutrient compositions. The study will assess the effectiveness of these state specific CSAM interventions.

**Methods:**

The longitudinal quasi-experimental study will be undertaken in two purposively selected blocks of one district each in the four intervention states and one comparison state. From each state, 200 SAM children identified using weight-for-length/height z-score (WHZ) < **−** 3 criteria will be enrolled in the study. Their anthropometric data and skinfold thickness will be taken on admission, at sixth week and at discharge by trained field investigators. Other child details, incidence of morbidity and socio-economic details will be collected on admission. To assess food consumption pattern including consumption of locally produced nutrient dense food supplements, dietary assessment, using 24-**h** dietary recall will be conducted on admission, at sixth week and at discharge. In addition, body composition parameters will be assessed for a sub-set of children using bio-electrical impedance analysis on admission and at discharge to analyse changes in total body water, fat-free mass, and fat mass. Post discharge, all study participants will be followed up monthly until 6 months. Atleast 10% of the sample will be checked for quality assessment.

The study’s primary outcome is cure rate defined as children attaining WHZ **≥** -2. Secondary outcomes include mean weight gain, mean length of stay, body composition parameters, relapse and mortality rates. Additionally, process evaluation and cost effectiveness analysis will be conducted.

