## Background

Severe Acute Malnutrition (SAM) is defined as a weight-for-height/weight-for-length z-score < − 3 (WHZ < -3) and/or mid upper arm circumference (MUAC) < 115 mm and/or clinical signs of bilateral pitting edema in children aged 6–59 months [1]. Globally, approximately 50 million under-five children suffer from wasting (WHZ < -2). India is home to approximately 18.3 million wasted children, representing 37% of the global burden of wasting. Of this, approximately 8 million children are severely wasted (WHZ < -3) [2]. The two national surveys have shown worsening of child wasting and severe wasting conditions in India [3, 4]. A recent pooled-analysis of existing community cohort studies has shown that mortality risk in severely wasted children was 11.6 times higher than in children without severely wasted [5]. In India, evidence also shows that around 20% of all deaths of children aged under-five years were due to wasting [6]. Other studies conducted in Bangladesh [7] and Latin America [8] have also found strong nutrition-mortality linkage among under-five children. Early identification and treatment before development of medical complications is essential to prevent mortality among SAM children.

The World Health Organization (WHO) recommends community-based management of acute malnutrition (CMAM) for early identification and treatment of children with SAM with no medical complications. CMAM includes community outreach for screening of children for SAM, outpatient management of uncomplicated SAM children through provision of ready-to-use therapeutic food (RUTF) and antibiotics, and in-patient treatment of medically complicated SAM children [9]. Evidence shows that community-based treatment program identifies and treats uncomplicated SAM children much before they develop any medical complications [10]. It also provides higher coverage through a regular community based screening process and complete treatment by enabling the child to be fully cured. It also has advantage over the facility-based treatment as there are poor cultural acceptances, chances of hospital-acquired infections and high relapse rates in the facility based treatment [11].

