The effectiveness of CMAM programme is primarily measured as proportion of children cured or recovered, which is defined as a child achieving WHZ ≥ -2 and/or MUAC ≥125 mm and through other measures like the rate of weight gain, time to recovery, defaulter rate, relapse rate and mortality rate. Sustainability of recovery has long been ignored in the outcomes of SAM treatment as primary focus of treatment was on reducing mortality from SAM. However, in recent years, implementers have begun to consider the extent to which treatment enables a recovery in both short and long terms [12].

SAM is clinically characterized by loss of muscle and fat tissue, reflecting an inadequate intake of energy and protein relative to body requirements. It also has a broader range of pathophysiological changes which are associated with reduced function of the body, specifically metabolic function, oxidative stress, cardiac function, hepatic function, enteropathy, renal and brain function [13]. Nutritional recovery of young children is typically gauged by short-term weight gain. However, an increase in weight does not necessarily reflect an increase in fat-free mass (FFM) as weight gain following severe illness has been shown to be secondary to gains in fat mass (FM) rather than FFM. Despite accounting for height and weight, body mass index (BMI) also does not accurately reflect FFM, as individuals with similar BMI can have significant variations in FFM [14]. Hence, it becomes important to additionally assess body composition (such as FM, FFM and total body water) to evaluate whether these parameters among rehabilitated SAM children are comparable with the normal children however, this has been done in very limited studies. Skinfold thickness and assessment of body composition by bio-electrical impedance analysis (BIA) is a better indicator of energy reserves. Skinfold measurements- tricep and sub-scapular, arm muscle area (AMA) and arm fat area (AFA) provide a simple, easy, and quick yet highly informative assessment of fatness in most patients. The analysis of body composition by BIA method produces estimates of total body water (TBW), fat-free mass (FFM), and fat mass (FM) by measuring the resistance of the body as conductor to a very small alternating electrical current or by administration of radioactive isotope [15, 16]. Application of the combination of these methods may reduce the likelihood of misdiagnosis of high or low lean mass [17].

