### Intervention strategy

In general, the State Governments of Telangana, Madhya Pradesh, Odisha and Chhattisgarh will implement community-based management of SAM (CSAM) programme adapted from the WHO guidelines, in addition to the existing government nutrition promotion interventions. The approach will incorporate active and/or passive case-finding and screening for severe wasting by government frontline nutrition and health workers. For uniformity, children with WHZ < -3 will be categorized as experiencing SAM. SAM children will further undergo medical examinations and appetite test to identify complicated and uncomplicated cases. All complicated cases will be referred to the nearest nutritional rehabilitation centres (NRCs) for in-patient management. All uncomplicated cases will be enrolled in the CSAM programme for their community-based management in *anganwadi centres*. While the program’s primary focus is on treatment of children who are severely wasted, key activities also include regular follow up of all enrolled children at the *anganwadi centers*, counseling of caregivers on infant and young child feeding (IYCF), safe water, sanitation and hygiene practices, family planning and child care practices, promotion of vaccinations, appropriate referrals of sick children to NRCs or public health facilities and post discharge follow up. SAM children enrolled in the programme will also be given locally produced nutrient dense food supplements, antibiotics, anthelminthic and micronutrient supplements. Key aspects of the state specific CSAM programme are presented in Table 1. Detailed description of the state specific CSAM protocols and nutritional content of each locally produced nutrient dense food supplement is provided in Additional file 1. In the comparison area, where no CSAM intervention is being implemented, SAM children identified and enrolled in the study will receive the existing government nutrition promotion interventions. The existing program includes provision of double quantity of Take Home Ration (THR)^1^ for severely underweight children (which covers most of SAM children) and identification and referral of SAM children to Malnutrition Treatment Centres (MTCs).

**Table 1 Tab1:** Key aspects of the CSAM protocol that vary per state assessed

States	Screening & Identification	Admission criteria	Maximum treatment duration	Discharge criteria	Nutrient dense food	Post-discharge Follow up

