#### Secondary research questions

Do state specific CSAM programmes help recovery of a SAM child, as defined by body composition parameters such as fat mass by skinfold thickness and fat free mass, body water by BIA, in each of the four intervention states?What is the relationship between anthropometry and body composition measures in a child suffering from SAM, in each of the five states?Do state specific CSAM programme provide better outcomes in terms of recovery, defaulting, death, length of stay and average weekly weight gain, compared to existing evidence from India?Which of the CSAM programme provides best rate of recovery 6 months after exit from the programme, defined by the relapse and mortality rates?

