### Selection of study samples

In each of the CSAM intervention states, 200 SAM children aged 6–59 months identified using WHZ < -3, who will be enrolled in the CSAM programme and who do not have any medical complication and pass the appetite test will be enrolled in the study. Similarly, in the comparison state, 200 SAM children aged 6–59 months will be identified using WHZ < -3 by the Field Investigators and enrolled in the study, who do not have any medical complication and pass the appetite test. Children identified between October’ 2020 and December’ 2020 will be enrolled in the study.

We will exclude SAM children with presence of emergency signs, edema, high fever, cough with fast breathing and known secondary SAM cases like neurological diseases such as cerebral palsy, TB, HIV congenital heart defects, congenital structural defects and cleft palate. However, if any child enrolled in the study develops any medical complication later during the course of the study, s/he will be referred to inpatient care but continued to be part of the study.

The sub-set of children (first 50% of the enrolled children i.e. 100 children in each state) with weight at enrollment > 5 kg will be selected for body composition, as the BIA machine can only give accurate measurement for children with weight > 5 kg. So in total, 500 children will be selected for studying their body composition in the five study states.

For identifying eligible study participants in the CSAM intervention states, SAM children to be identified and enrolled by the frontline workers according to the identification criteria of the state specific CSAM programme from each of these selected *anganwadi centres*, will be rechecked by field investigators within 72 h and those children who will qualify on the basis of inclusion and exclusion criteria of the study, will be enrolled in the study. Similarly, in the comparison state, Field Investigators will identify eligible study participants and enroll in the study. Field Investigators will then approach caregivers of the children to explain the study and seek their written consent for participation. They will also be asked for permission to follow-up their children during the treatment phase and for 6 months’ post discharge in order to measure the impact of the interventions.

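### The study's cure endpoint does not require absence of oedema, so weight from new fluid can be scored as recovery

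*Protocol article*

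**What the plan says.** All places are in the protocol article.

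- **Endpoint (abstract, Methods).** The "primary outcome is cure rate defined as children attaining WHZ" at or above −2. Nothing else is required.
- **General definition of SAM (Background).** Besides WHZ < −3, it names "mid upper arm circumference (MUAC) < 115 mm and/or clinical signs of bilateral pitting edema".
- **Definition used in the study (Intervention strategy).** "For uniformity, children with WHZ < -3 will be categorized as experiencing SAM".
- **Entry (Selection of study samples).** "We will exclude SAM children with presence of emergency signs, edema, high fever", among other conditions. The same section says that an enrolled child who later develops a medical complication is referred for inpatient care but remains in the study.
- **Measurements (Data collection, cleaning and storage; Table 2).** Recovery is judged from length or height, weight and two skinfolds, at admission, week 6 and discharge. After discharge there is monthly anthropometry for six months, with skinfolds and body composition repeated at month six. Oedema appears in no row of Table 2.
- **Analysis (Data analysis).** All enrolled children are included, and recovery is the event in the Cox model.

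**The concern.** WHZ compares weight with length and cannot tell tissue from fluid. A child who becomes oedematous gains weight while getting worse, so the error has a direction: it moves a deteriorating child towards cured. The same error would carry into the Cox model and the weight-gain outcome. It would also affect relapse, so far as relapse is read from the monthly weights and lengths. Secondary research question 4 ranks the programmes partly on relapse.

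What is at stake is whether a cure in this study always means recovery. Without a recorded check, the investigators could not show that the number of such misclassified children was zero.

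**Working it through.** **Following one child through the stated rules**

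1. *Entry.* Oedema excludes, so every enrolled child starts without it. Only new oedema matters.
2. *Treatment period.* If oedema develops, the child may be referred, but stays in the study and in the analysis.
3. *Exit.* The only test is WHZ ≥ −2. If fluid has lifted the weight past that limit, the rule returns cured. No sentence withholds that status.
4. *After discharge.* The monthly visits collect anthropometry. If oedema develops then, the added weight raises WHZ, so a WHZ-based reading would not show a relapse.

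The asymmetry lies within the Methods: freedom from oedema is needed to enter but not to be called cured. The one premise from outside the documents is that oedema fluid adds weight.

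**The plan's own figure first**

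Inputs from Sample size: cure 50% against 25%, significance level 5%, power 80%, design effect 1.5, attrition 20%, stated n = 100 per age group per state. I assume a two-sided test, unpooled variance and inflation by 1.2.

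n = (1.95996 + 0.84162)² × (0.50 × 0.50 + 0.25 × 0.75) / 0.25² = 7.849 × 0.4375 / 0.0625 = 54.94

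54.94 × 1.5 × 1.2 = 98.9, rounded up to 99, against the stated 100. The figure is reproduced. It does not depend on the oedema question.

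**How many children could be affected**

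The documents give no frequency. Assume that 0–3% of enrolled children are oedematous and scored as cured:

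- 0.00 × 200 = 0 and 0.03 × 200 = 6 children per state, so 0–3 percentage points.
- The upper figure requires every new case to gain enough fluid to cross −2 and to be oedematous when scored.
- Six children are 6% of the 100 cures expected in an intervention state (0.50 × 200), or 12% of the 50 expected in the comparison state (0.25 × 200).

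**Effect on the planned difference**, taking 50% and 25% as the rates on WHZ alone and removing 3 points of false cures:

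| False cures occur in | Cure rates after correction | Difference |
|---|---|---|
| both arms equally | 47% vs 22% | 25 points |
| intervention state only | 47% vs 25% | 22 points |
| comparison state only | 50% vs 22% | 28 points |

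**Effect on power**, if a fixed share of WHZ-based cures is reclassified as not cured in both arms (pooled formula). The effective numbers per arm are 160 / 1.5 = 106.7 for a whole state and 80 / 1.5 = 53.3 for one age group:

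| Share of cures reclassified | Cure rates | Power, 200 per state | Power, one age group |
|---|---|---|---|
| 0% | 50% vs 25% | 97.0% | 76.8% |
| 2% | 49% vs 24.5% | 96.5% | 75.4% |
| 5% | 47.5% vs 23.75% | 95.7% | 73.3% |
| 10% | 45% vs 22.5% | 94.1% | 69.6% |

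These rows are illustrations. Nothing in the documents says which one is realistic.

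**The case against.** The strongest reply is that WHZ alone is a stated and consistent choice. The Intervention strategy section narrows SAM to WHZ < −3 for this study, enrolment uses the same index, and in Table 1 all four programmes admit and discharge on it. The Background describes recovery in such programmes as one "which is defined as a child achieving WHZ ≥ -2 and/or MUAC ≥125 mm", which WHZ alone satisfies. All of this stands. It rules out calling the endpoint a contradiction of the study's definition of SAM. It does not explain why oedema bars entry and is then ignored at exit.

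A second reply is that silence in Table 2 proves little. The table has no oedema row at admission either, although oedema must be assessed there, and it omits the appetite test. Enrolled children are seen regularly at the anganwadi centres, illness history is taken again at discharge, and the state protocols are in an additional file that is not shown. So oedema may well be looked for in practice. But the gap is in the scoring rule: an observation changes nothing unless the endpoint uses it, and the article ties none of these sources to cure.

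Third, body water is measured by bio-electrical impedance at admission and discharge. That covers 100 of 200 children per state, and it too has no link to the cure status.

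Fourth, the size is assumed, may be zero, and is small against 25 points. This is correct and limits the weight of the point.

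**Conclusion.** The point holds for oedema. As written, the cure rule can score fluid gain as recovery, and monthly anthropometry can miss a relapse with oedema. The frequency is unknown. Under the assumed 0–3%, it is 0–6 children per state and at most 3 percentage points, which would not overturn a true difference of 25. It is a cheap improvement in endpoint validity and does not threaten the main comparison.

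A reader might infer two stronger points that the documents do not support:

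- *That a child at WHZ ≥ −2 with MUAC below 115 mm still has SAM by the study's definition.* The three-part definition is general background. The study enrols and scores on WHZ, and the Background accepts WHZ alone for recovery. Leaving out MUAC is therefore not an error.
- *That secondary research question 3, which asks for better results "compared to existing evidence from India", compares unlike criteria.* The article quotes published recovery rates of 46.7 to 57.4% without giving the cure criteria behind them, so a mismatch cannot be shown.

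**What to change.** Change the study's endpoint and data form only. The programmes' discharge and treatment rules are outside this point and stay unchanged.

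1. Add one field, bilateral pitting oedema yes/no, to the week-6, discharge and monthly post-discharge study visits.
2. Define cure for the study as WHZ ≥ −2 with no bilateral pitting oedema at the same visit. A child whom the programme discharges on WHZ but who has oedema is then counted as discharged and not cured.
3. Count bilateral oedema found after discharge as relapse.
4. Report the number of children whose status changes under this rule, by state, so that readers can see whether it was zero.

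The cost is a few seconds at visits where the field investigator already measures the child, and possibly a slightly lower cure rate. The article says that recruitment is under way. Because oedema excludes at entry, no baseline data need to be collected again. Visits completed before the change should be reported as not assessed for oedema.

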**Discussion:**

There is a shortage of robust evidence regarding the effectiveness of locally produced nutrient dense food supplements provided as part of the CSAM intervention in India. This study will contribute to evidence on effective strategies to manage children with uncomplicated SAM in India. The study protocol has all necessary ethical approvals. Written informed consent will be obtained from caregivers of the children.

**Trial registration:**

The study is registered with Clinical Trial Registration of India (Registration No.: CTRI/2020/09/028013) Date of registration 24/09/2020.

**Supplementary Information:**

The online version contains supplementary material available at 10.1186/s40795-021-00489-1.

## Background

Severe Acute Malnutrition (SAM) is defined as a weight-for-height/weight-for-length z-score < − 3 (WHZ < -3) and/or mid upper arm circumference (MUAC) < 115 mm and/or clinical signs of bilateral pitting edema in children aged 6–59 months [1]. Globally, approximately 50 million under-five children suffer from wasting (WHZ < -2). India is home to approximately 18.3 million wasted children, representing 37% of the global burden of wasting. Of this, approximately 8 million children are severely wasted (WHZ < -3) [2]. The two national surveys have shown worsening of child wasting and severe wasting conditions in India [3, 4]. A recent pooled-analysis of existing community cohort studies has shown that mortality risk in severely wasted children was 11.6 times higher than in children without severely wasted [5]. In India, evidence also shows that around 20% of all deaths of children aged under-five years were due to wasting [6]. Other studies conducted in Bangladesh [7] and Latin America [8] have also found strong nutrition-mortality linkage among under-five children. Early identification and treatment before development of medical complications is essential to prevent mortality among SAM children.

The World Health Organization (WHO) recommends community-based management of acute malnutrition (CMAM) for early identification and treatment of children with SAM with no medical complications. CMAM includes community outreach for screening of children for SAM, outpatient management of uncomplicated SAM children through provision of ready-to-use therapeutic food (RUTF) and antibiotics, and in-patient treatment of medically complicated SAM children [9]. Evidence shows that community-based treatment program identifies and treats uncomplicated SAM children much before they develop any medical complications [10]. It also provides higher coverage through a regular community based screening process and complete treatment by enabling the child to be fully cured. It also has advantage over the facility-based treatment as there are poor cultural acceptances, chances of hospital-acquired infections and high relapse rates in the facility based treatment [11].

The effectiveness of CMAM programme is primarily measured as proportion of children cured or recovered, which is defined as a child achieving WHZ ≥ -2 and/or MUAC ≥125 mm and through other measures like the rate of weight gain, time to recovery, defaulter rate, relapse rate and mortality rate. Sustainability of recovery has long been ignored in the outcomes of SAM treatment as primary focus of treatment was on reducing mortality from SAM. However, in recent years, implementers have begun to consider the extent to which treatment enables a recovery in both short and long terms [12].

SAM is clinically characterized by loss of muscle and fat tissue, reflecting an inadequate intake of energy and protein relative to body requirements. It also has a broader range of pathophysiological changes which are associated with reduced function of the body, specifically metabolic function, oxidative stress, cardiac function, hepatic function, enteropathy, renal and brain function [13]. Nutritional recovery of young children is typically gauged by short-term weight gain. However, an increase in weight does not necessarily reflect an increase in fat-free mass (FFM) as weight gain following severe illness has been shown to be secondary to gains in fat mass (FM) rather than FFM. Despite accounting for height and weight, body mass index (BMI) also does not accurately reflect FFM, as individuals with similar BMI can have significant variations in FFM [14]. Hence, it becomes important to additionally assess body composition (such as FM, FFM and total body water) to evaluate whether these parameters among rehabilitated SAM children are comparable with the normal children however, this has been done in very limited studies. Skinfold thickness and assessment of body composition by bio-electrical impedance analysis (BIA) is a better indicator of energy reserves. Skinfold measurements- tricep and sub-scapular, arm muscle area (AMA) and arm fat area (AFA) provide a simple, easy, and quick yet highly informative assessment of fatness in most patients. The analysis of body composition by BIA method produces estimates of total body water (TBW), fat-free mass (FFM), and fat mass (FM) by measuring the resistance of the body as conductor to a very small alternating electrical current or by administration of radioactive isotope [15, 16]. Application of the combination of these methods may reduce the likelihood of misdiagnosis of high or low lean mass [17].

Most of the evidence on the effectiveness of the CMAM programme comes from observational studies conducted in emergency settings in Africa [18]. Also, these evidence of effectiveness are largely gauged through anthropometric parameters and not through body composition. While CMAM has been adopted by many countries worldwide, India is yet to have a formal national guideline for CMAM strategy due to lack of consensus on using RUTF in the programme. There are a few pilot studies on CMAM conducted in India using the WHO recommended RUTF for assessing efficacy of the community based programmes. Such studies with RUTF achieved recovery rates ranging from 46.7 to 57.4% [19–23] however, beyond anthropometric parameters these studies did not report any finding related to the child’s body composition.

